## Abstract

**Background:**

Self-monitoring of hypertension with self-titration of antihypertensives (self-management) results in lower systolic blood pressure for at least one year. However, few people in high risk groups have been evaluated to date and previous work suggests a smaller effect size in these groups. This trial therefore aims to assess the added value of self-management in high risk groups over and above usual care.

**Methods/Design:**

The targets and self-management for the control of blood pressure in stroke and at risk groups (TASMIN-SR) trial will be a pragmatic primary care based, unblinded, randomised controlled trial of self-management of blood pressure (BP) compared to usual care. Eligible patients will have a history of stroke, coronary heart disease, diabetes or chronic kidney disease and will be recruited from primary care. Participants will be individually randomised to either usual care or self-management. The primary outcome of the trial will be difference in office SBP between intervention and control groups at 12 months adjusted for baseline SBP and covariates. 540 patients will be sufficient to detect a difference in SBP between self-management and usual care of 5 mmHg with 90% power. Secondary outcomes will include self-efficacy, lifestyle behaviours, health-related quality of life and adverse events. An economic analysis will consider both within trial costs and a model extrapolating the results thereafter. A qualitative analysis will gain insights into patients’ views, experiences and decision making processes.

**Discussion:**

The results of the trial will be directly applicable to primary care in the UK. If successful, self-management of blood pressure in people with stroke and other high risk conditions would be applicable to many hundreds of thousands of individuals in the UK and beyond.

**Trial Registration:**

ISRCTN87171227

## Background

The potential benefit from optimal blood pressure (BP) lowering in patients at high cardiovascular risk following stroke or TIA, coronary heart disease or with diabetes or CKD is large. The PROGRESS trial demonstrated that blood pressure lowering is beneficial in reducing risk of stroke amongst both hypertensive and non-hypertensive individuals with a history of stroke or TIA [1,2]. For people with coronary heart disease, blood pressure lowering has the same risk reduction as in those without coronary heart disease however the higher absolute risk in CHD means that for a given blood pressure reduction the absolute benefits are greater [3]. The Hypertension Optimal Treatment trial showed no difference in outcome for diastolic blood pressure targets below 90mmHg, apart from in people with diabetes for whom the 80mmHg target group did better. The blood pressure trialists collaborative have shown similar relative risk reductions from blood pressure lowering in diabetes compared to other groups, again with higher absolute risk reductions. In subgroup analyses of the HOPE study, people with chronic kidney disease (CKD) received equivalent benefit from ramipril as those without kidney disease [4].

Guidelines for the various at risk groups vary in terms of recommendations for blood pressure lowering. The National Clinical Guideline for stroke [5] and the British Hypertension Society (BHS) [6] recommend that unless there is bilateral carotid artery stenosis, the target blood pressure for secondary prevention of stroke and TIA should be 130/80mmHg. NICE guidelines for diabetes, suggest a lower blood pressure target than recommended for essential hypertension of 140/80mmHg (130/75mmHg in cases of proteinuria). For coronary heart disease, standard blood pressure targets are recommended (≤ 140/90 mmHg), and for chronic kidney disease NICE also recommend a target of 140/90 mmHg, unless there is accompanying diabetes or proteinuria (ACR > 70 mg/mmol) in which case the target drops to 130/80 mmHg. The BHS guidelines however, suggest a target of <130/80 mmHg for stroke/ TIA, diabetes, CKD3 (without proteinuria), CHD and MI allowing uniformity across the range of high risk groups [6].

Data from national and international surveys suggest that blood pressure control is sub-optimal [7]. Novel interventions are therefore needed to improve this and as most blood pressure management is undertaken in primary care, where hypertension is the commonest long term condition seen by GPs, it is appropriate that interventions are delivered in this setting. The TASMINH2 trial [8,9] found that self-management of hypertension resulted in significantly lower (5.4mmHg) systolic blood pressure after one year compared to usual care. However, the study included few people in high risk groups such as diabetes or CKD, in whom the effect size appeared to be smaller and included telemetry which is not available in daily practice in the NHS.

Self-management can encompass a wide range of behaviours in addition to medication titration and monitoring of symptoms, such as an individual’s ability to manage physical, psychosocial and lifestyle behaviours related to chronic illness [10]. Self-efficacy, which is a person’s confidence to be able to carry out behaviours to achieve a desired goal, has been found to be the strongest predictor of a person’s ability to change risky health behaviours by taking action, and an important characteristic for successful self-management [11]. It is unclear what the relationship is between self-monitoring of blood pressure, self-efficacy and health behaviour modification; it is possible that the self-monitoring aspect provides feedback to the individual about their blood pressure of which they would otherwise be unaware. This in turn may promote self-management of health behaviours in those with higher levels of self-efficacy. These behavioural aspects require further study.

Therefore, the aim of this trial is to determine whether the benefits from blood pressure lowering observed in the TASMINH2 trial will also be observed in a population of people at high cardiovascular risk without using telemetry and to assess further the mechanism behind any change in blood pressure observed. The TASMIN-SR trial sets out to investigate whether self-management is effective and cost effective in people with stroke and other high risk conditions.

## Methods/Design

### Study aims, research questions, and outcomes

The primary aim of TASMIN-SR is to compare self-management with usual care in the control of hypertension in patients with stroke and other at-risk conditions.

The trial has four main research questions:

1. Does self-management of blood pressure result in better control of blood pressure in people with stroke and other at-risk conditions compared to usual care?

2. Is self-management of blood pressure in people with stroke and other at-risk conditions achievable in routine practice and is it acceptable to patients?

3. What is the relationship between self-management of blood pressure, self-efficacy, lifestyle behaviours, patients’ attitude to health and health care and use of other self-care strategies in people with stroke and other at-risk conditions?

4. Is self-management of blood pressure in people with stroke and other at-risk conditions cost effective?

The primary outcome of the trial will be the difference in office systolic blood pressure (mmHg) at 12-month follow-up between intervention and control adjusted for baseline blood pressure and co-variates. Secondary outcomes (also adjusted for baseline and co-variates) will include:

–  Difference in office SBP at 6-month follow-up between intervention and control

–  Difference in office DBP at 6 and 12-month follow-up between intervention and control

–  Percentage time in target BP range

–  Difference in pulse rate

–  Difference in self-management self-efficacy

–  Difference in lifestyle behaviours

–  Difference in health-related quality of life

–  Difference in BP measurement preference

–  Difference in anxiety

–  Difference in attitudes to health and healthcare

–  Difference in use of other self-management strategies

–  Reasons for non-participation

–  Adverse events (including cardiovascular events and death)

–  In addition there will be a qualitative analysis and health economic modelling.

### Study design and setting

TASMIN-SR is a pragmatic, primary care based, unblinded, randomised controlled trial (with embedded economic and qualitative analyses) of self-management of BP consisting of self-monitoring with self-titration of anti-hypertensive medication in people with stroke and other at-risk conditions.

### Ethical considerations

Ethical approval has been obtained from North West – Greater Manchester East ethics committee (reference: 10/H1013/60). Site specific R&D approval will be obtained from the relevant Primary Care Trusts.

### Trial interventions

Usual care will consist of the participant seeing their General Practitioner (GP) and/or nurse for routine BP measurement and/or adjustment of medication at the discretion of the health professional.

Self-management will consist of self-monitoring of BP with self-titration of medication following a predetermined 3-step plan, dependant on the self-monitored BP readings.

#### Blood pressure self-monitoring

Participants will be trained to self-monitor BP using an automated sphygmomanometer. Patients will self-monitor BP for the first week of each month of the study, and will take measurements in the morning. Two seated BP readings will be taken, with a five-minute rest period between them. The second of these readings will be used to determine if medication requires altering. Participants will be provided with a guideline that contains simple colour coded instructions. Very high or very low readings that persist when a third reading is taken five minutes after the second reading will require the participant to contact their practice for advice and potentially will need checking. Four or more above target readings in two consecutive weeks of measurement will require a change in medication. Readings within target range will simply require further monitoring the following month.

#### Target blood pressure

Blood pressure targets will be based on The British Hypertension Society guidelines [6] and Joint British Societies Guidelines [12] that suggest that the BP for patients with stroke/TIA, diabetes (in the absence of proteinuria), CKD, CHD, and MI should be <130/80 mmHg. The BHS suggest that for home monitoring this target should be adjusted by 10/5 mmHg, resulting in a target of <120/75 mmHg [6].

#### Communication of home readings

Participants will complete a simple form each month to record their daily BP readings and colour coding. These forms will be used to determine any action that is required at the end of the measurement week, including whether a medication change is required. The form will be printed on three-part non-carbon copy paper to allow one copy to be kept by the patient, one returned to the research team, and one posted to the GP should a medication change be required. Reply paid envelopes will be provided for this purpose. At follow-up, data from participants’ BP machines will be uploaded onto a database so that the research team has an electronic copy.

#### Self-titration of medication

Each intervention patient will be given an individually tailored three-step management plan through which to adjust medication according to measured BP. Each step will represent a single medication change (additional medication or increased dose) that will be made following two consecutive months of raised readings. Medication choice will remain at the discretion of the GP who will be provided with an algorithm summarising the national clinical guidelines for advice on hypertension. If patients use all three steps of their management plan they will return to their GP and an additional two-step plan will be devised. This will not be until at least eight months into the trial, assuming no very high or very low readings, so a three-step plan should be sufficient. Any additional monitoring (for instance blood tests or urinalysis) will be the responsibility, and at the discretion, of the GP.

### Non-participation

Included with the letter of invitation to take part in the trial, will be a form for people to voluntarily return should they wish to decline the invitation. This will ask for basic demographic details as well as their reasons for wishing to decline.

### Study population

The study population will comprise people with stroke/TIA, diabetes, CKD3, CABG, MI or angina, with poorly controlled hypertension managed in primary care. Eligibility criteria will be age above 35, have had a diagnosis of stroke/TIA, diabetes, CKD3, MI, angina, or CABG, and clinic blood pressure greater than 130/80. Exclusion criteria will be inability to self-monitor (such as dementia or score of >10 on the short orientation memory concentration test), postural hypotension (systolic BP drop > 20 mmHg), prescribed more than three anti-hypertensive medications, taking part in a current BP study or previously having taken part in TASMINH2 [8], terminal disease, pregnant, BP not managed by GP, and acute cardiovascular event in the previous three months.

Eligible patients will be identified from general practices via the UK Primary Care Research Network. Trained practice nurses will identify potentially eligible patients by searching practice-based registers for patients having a Read Code of stroke/TIA, diabetes, CKD3, Angina, CABG, or MI and whose last systolic BP measurement was greater than 145 mmHg (BP readings are often lower when measured by research teams, so a higher BP at invitation increases the likelihood of BP readings falling within the suitable range [13].) GPs will be asked to check the generated lists and remove patients who have a terminal illness, are pregnant, or who are thought to be unsuitable for the study.

Participants who withdraw will not be replaced, but asked if they are prepared to continue to attend follow-up clinics.

### Randomisation

Patients will be randomised to either usual care or self-management using an internet based system with telephone backup. Minimisation will be used to take into account practice, gender, age, high risk group (CVD, diabetes, CKD3, CHD) and baseline BP.

### Study clinics and flow through study

At baseline, all patients will attend a clinic at which the study will be explained, informed consent gained, height, weight, and BP measurements taken, and questionnaires regarding demographics, past medical history, BP measurement method preference, use of self-management strategies, attitudes to health and healthcare completed, and baseline economic data collected (Table 1). Measurement of blood pressure will use a validated automated electronic sphygmomanometer (BP TRU BPM 200; BP TRU Medical Devices; Coquitlam, BC, Canada) [14]. After five minutes of rest, six seated blood pressure readings will be taken at 1-minute intervals, of which the mean of the 2^nd^ and 3^rd^ reading will comprise the primary outcome. Patients will then be randomised to either usual care or self-management. All patients will be given a diary to assess daily lifestyle behaviours and self-management self-efficacy which they will be asked to complete everyday for one week starting the first Monday of the month after their baseline appointment. Patients randomised to usual care will be asked to book an appointment for a routine blood pressure check and medication review with the study GP. Patients randomised to self-management will be asked to make an appointment with the research team for a training session on how to monitor their BP. Participants will be asked to practice at home for a week before returning for a second training session covering the self-titration aspect of the intervention. If necessary, a third training session will be offered for additional support. Following successful completion of the training, patients will be asked to make an appointment with the study GP at their practice for a routine BP check and to devise a three step titration plan for any potential medication changes. Patients who are unable to complete all aspects of the training will be given the option to self-monitor without self-titration of medications.

**Table 1 T1:** Data collection throughout the trial

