**Baseline only:**	
1	Demographic questions: including age, race, marital status, occupation, and education
2	Duration of hypertension
3	Past medical history
4	Contraindications to anti-hypertensives
5	Short orientation memory test [15]
6	Height
7	Joint pain questionnaire [16]
Baseline and follow-up:	
1	New medical history (in last 6/12 months)
2	Blood pressure (sitting plus standing at baseline)
3	Current anti-hypertensive medications
4	Weight
5	Symptom section of the IPQ [17]
6	Partners in health scale [18]
7	Short-form of the State-Trait Anxiety Inventory [19]
8	EQ-5D [20]
9	Use of complementary and alternative medicine and self-tests [21]
10	BP measurement preference
11	Attitudes to health and healthcare [22]
Lifestyle diaries	
1	Simple lifestyle indicator questionnaire (SLIQ) [23]
2	The dietary quality score [24]
3	Self-efficacy (adapted diabetes self-efficacy scale) [25]

Patients will be asked to attend two follow-up clinics at 6- and 12-months post-randomisation. Each clinic will be timetabled for no more than one hour, during which patients will have their BP and weight measured by the research team and will be asked to complete a questionnaire similar to the one completed at baseline. At the 12 month follow up, participants will also be given a blank postcard and asked to write a few sentences about their experience of the trial. Additionally, the research team will check that patients in the intervention arm are using the blood pressure monitors correctly. Flow through the trial is summarised in Figure 1.

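### The only early measurement described for self-efficacy and lifestyle is a diary completed after unblinded randomisation; used as the baseline covariate, it would bias these secondary comparisons

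*Protocol article*

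**What the plan says.** The section on study clinics and flow sets the order of events at the baseline visit. Consent, measurements and clinic questionnaires come first. After that, "Patients will then be randomised to either usual care or self-management". The next sentence reads "All patients will be given a diary to assess daily lifestyle behaviours and self-management self-efficacy", and the diary is one "which they will be asked to complete everyday for one week starting the first Monday of the month after their baseline appointment".

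Table 1 has three blocks: items at baseline only, items at baseline and follow-up, and the lifestyle diaries. The lifestyle questionnaire, the dietary score and "Self-efficacy (adapted diabetes self-efficacy scale" appear only in the diary block.

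The section on aims and outcomes introduces its list with "Secondary outcomes (also adjusted for baseline and co-variates) will include". The list contains "Difference in self-management self-efficacy" and a matching entry for lifestyle behaviours.

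The trial is described as unblinded. Between allocation and the start of self-titration, the self-management arm is to have a training session, a week of practice at home, a second session and a GP appointment. No dates are given for these steps or for later diaries.

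**The concern.** A baseline covariate is safe in a randomised comparison because allocation cannot have changed it. The first diary does not have that property. Patients know their arm when they complete it, and those in the self-management arm may already have been trained or be practising at home. Building confidence to self-manage is what such training would be expected to do, so an early difference in self-efficacy is plausible.

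Adjusting the 12-month comparison for a score that allocation has already moved no longer estimates the full effect of allocation. The results at stake are the self-efficacy and lifestyle outcomes and the part of research question 3 that rests on them. The Background also suggests that self-monitoring may change behaviour in people with higher self-efficacy. That is an effect-modification hypothesis and needs a score from before allocation. A later score mixes who the patient was with what the intervention has already done.

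**Working it through.** **1. The plan's own figures.** No stated figure bears on this point. The primary-outcome sample size reproduces: with two-sided alpha 0.05 (assumed, as it is not stated), n = 2 × (1.960 + 1.282)² × (17/5)² = 243 per group, and 243/0.90 = 270 per group, 540 in total. The illustration below borrows 243 per arm.

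**2. How long after randomisation is the diary?** Randomisation takes place at the baseline appointment. The diary starts on the first Monday of the month after it. Taking this as the next calendar month and enumerating every weekday appointment over ten years:
- range 3 to 35 days, median 19, mean 18.8;
- at least 7 days for 88% of dates and at least 14 days for 65%.

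If the phrase means the next first Monday after the appointment, and every calendar day can be a clinic day, the range is 1 to 35 days (mean 15.9). On either reading the diary always follows allocation.

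**3. Which score can be the baseline?** There are two possibilities.
- The first diary is the baseline. The covariate then post-dates allocation.
- It is not. The text then describes no baseline on these scales, and the promised adjustment cannot use the outcome's own earlier score.

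**4. Effect of adjusting for the diary.** Let T be the true arm difference at follow-up, e the arm difference that allocation has produced by the diary week, and b the within-arm slope of follow-up score on diary score. Analysis of covariance estimates

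(difference at follow-up) − b × (difference in diary), with expectation **T − b × e**.

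The document gives no value for T, e or b. For illustration, take T = 0.30 SD:

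| b | e = 0 | e = 0.10 SD | e = 0.20 SD | e = 0.30 SD |
|---|---|---|---|---|
| 0.3 | 0.30 | 0.27 (10% lost) | 0.24 (20%) | 0.21 (30%) |
| 0.5 | 0.30 | 0.25 (17%) | 0.20 (33%) | 0.15 (50%) |
| 0.7 | 0.30 | 0.23 (23%) | 0.16 (47%) | 0.09 (70%) |

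Simulation with 400,000 patients agrees: 0.200 for b = 0.5, e = 0.20; 0.161 for b = 0.7, e = 0.20; 0.147 for b = 0.5, e = 0.30. A negative e reverses the bias and inflates the estimate.

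**5. Bias against precision.** Assume 243 complete diaries per arm, unit SD and residual SD √(1 − b²). With b = 0.5, power for the diary-adjusted analysis is 97% at e = 0, 89% at e = 0.10, 72% at e = 0.20 and 48% at e = 0.30. Leaving the diary out gives 0.30 × √(243/2) = 3.31; 3.31 − 1.96 = 1.35; power 91%. At this slope, even e = 0.10 SD cancels the gain from adjustment. At b = 0.7 and e = 0.10 the adjusted analysis still has more power (94%), but for an estimate that is 23% too small.

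**The case against.** **The text never calls the diary the baseline.** This is true, and Table 1 keeps the diaries apart from the items labelled as baseline. The wording on adjustment follows directly after a sentence about baseline blood pressure and could refer back to it. It also heads a list that includes reasons for non-participation and adverse events, for which adjustment for the outcome's own baseline makes no sense. A statistical analysis plan may settle the covariates, and Figure 1 could not be consulted. The bias is therefore conditional on the diary being used as the baseline. The point still stands, because no other early score on these scales is described, and an analysis plan can drop a covariate but cannot create a measurement from before randomisation.

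**Training before the diary week is not scheduled.** This is also right: patients are asked to book it, and no interval is given. A reader might also infer that the diary coincides with self-monitoring, since "Patients will self-monitor BP for the first week of each month of the study". That holds only if calendar months are meant, and two training sessions, a practice week and a GP visit come first. Exposure is possible, not established. Knowledge of allocation, however, is certain.

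**The whole early effect would be lost.** A reader might infer this, but it does not follow. The amount removed is b × e, which equals the whole early effect only if b = 1 and is zero if there is no early shift. The case e = T is extreme.

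**Randomisation no longer protects research question 3.** This is too broad. A comparison of follow-up diary scores without the first diary as covariate remains fully randomised. The question also covers attitudes to health care and other self-care strategies, which are recorded at the clinic before allocation.

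**Conclusion.** The point holds in conditional form. The order and timing are stated explicitly: the first self-efficacy and lifestyle diary follows unblinded allocation by about 3 to 35 days for weekday appointments. If it serves as the baseline in the stated adjustment, the arm difference is shifted by b × e. Part of the effect is removed when the early shift is in the same direction as the final one, and nothing is lost when there is no early shift. The size cannot be derived from the document; the 10% to 70% range rests on assumed values of T, b and e. The diary is also unsuitable as a moderator for the self-efficacy hypothesis.

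This is a moderate issue, limited to the diary-based secondary outcomes and the related part of research question 3. Office systolic pressure, the sample size and the questionnaires completed at the clinic before randomisation are not affected.

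**What to change.** State in the sections on outcomes and on statistical analysis that:
- the first diary will not be used as a baseline covariate or as a moderator;
- follow-up diary scores will be compared with adjustment only for variables measured before randomisation, namely the minimisation factors and, if it is completed at the baseline clinic before allocation, the Partners in Health scale;
- the first diary will be reported as an early post-randomisation outcome.

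This takes a few sentences and needs no extra patients or visits. The cost is precision. In the illustration, if there were no early shift, power would fall from 93%, 97% and over 99% (b = 0.3, 0.5, 0.7) to 91%, less whatever the pre-randomisation covariates recover.

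Optionally, a short single-occasion form of the scales could be completed at the baseline clinic after consent and before randomisation. It adds a few minutes and supplies a valid covariate and moderator, but it is not the same instrument as a seven-day diary. Posting the full diary before the clinic is not recommended: it would collect research data before consent, including from the half of attenders whom the Recruitment section expects to be ineligible.
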